## Abstract

Balance and gait impairments, and consequently, mobility restrictions and falls are common in Parkinson’s disease (PD). Various cognitive deficits are also common in PD and are associated with increased fall risk. These mobility and cognitive deficits are limiting factors in a person’s health, ability to perform activities of daily living, and overall quality of life. Community ambulation involves many dual-task (DT) conditions that require processing of several cognitive tasks while managing or reacting to sudden or unexpected balance challenges. DT training programs that can simultaneously target balance, gait, visuomotor, and cognitive functions are important to consider in rehabilitation and promotion of healthy active lives. In the proposed multi-center, randomized controlled trial (RCT), novel behavioral positron emission tomography (PET) brain imaging methods are used to evaluate the molecular basis and neural underpinnings of: (a) the decline of mobility function in PD, specifically, balance, gait, visuomotor, and cognitive function, and (b) the effects of an engaging, game-based DT treadmill walking program on mobility and cognitive functions. Both the interactive cognitive game tasks and treadmill walking require continuous visual attention, and share spatial processing functions, notably to minimize any balance disturbance or gait deviation/stumble. The ability to “walk and talk” normally includes activation of specific regions of the prefrontal cortex (PFC) and the basal ganglia (site of degeneration in PD). The PET imaging analysis and comparison with healthy age-matched controls will allow us to identify areas of abnormal, reduced activity levels, as well as areas of excessive activity (increased attentional resources) during DT-walking. We will then be able to identify areas of brain plasticity associated with improvements in mobility functions (balance, gait, and cognition) after intervention. We expect the gait-cognitive training effect to involve re-organization of PFC activity among other, yet to be identified brain regions. The DT mobility-training platform and behavioral PET brain imaging methods are directly applicable to other diseases that affect gait and cognition, e.g., cognitive vascular impairment, Alzheimer’s disease, as well as in aging.

## Introduction

Disruption of frontostriatal circuits in Parkinson’s disease (PD) have been shown to be associated with gait impairments (Rochester et al., 2004; Rosenberg-Katz et al., 2015) and deficits in executive cognitive functions (Kudlicka et al., 2011; Olchik et al., 2017). It is now well established that gait and cognition are closely linked (Plotnik et al., 2011; Kelly et al., 2012; Callisaya et al., 2016). For example, community ambulation requires walking while also performing a variety of executive cognitive functions, such as navigating busy environments, managing complex terrains, searching for and tracking various visual targets, information processing of what is being seen, reading, etc. Unfortunately, both mobility skills and cognition are often affected in PD (Mak et al., 2014; Paul et al., 2014; Schneider et al., 2015).

The dual-task (DT) paradigm has been used in a number of studies to assess the magnitude of DT interference of cognitive load on gait function and vice versa in PD (Rochester et al., 2014; Heinzel et al., 2016; Penko et al., 2018). DT testing is considered representative of real-life situations, and provides better insight into functional capacity. The concept of motor automaticity has an important implication in the pathophysiology of PD related to mobility limitations and increased fall risk (Wu et al., 2015; Gilat et al., 2017). One model of executive cognitive functions presents the supervisory attentional system, which distinguishes between processing of non-routine, attentionally demanding activities vs. routine, automated tasks (Dirnberger and Jahanshahi, 2013). The role of the sensorimotor striatum has been equated with that of routine tasks, such as locomotion, that are usually performed automatically (Gilat et al., 2017). The increased attentional and information processing demands of DT-walking are presumed to reduce the already limited locomotor control of PD patients (Kang et al., 2005; Wu and Hallett, 2008), and this may result in greater gait variability/instability and a higher risk of falls.

Emerging evidence suggests that the decline in mobility function due to a combination of motor and cognitive impairment can be improved by DT training (Gregory et al., 2017). For example, virtual environments viewed during treadmill walking provides a task-orientated approach to DT-walking training (Mirelman et al., 2016). Maximizing participation is also a main goal of any exercise program. Long-term exercise programs are often fraught with low compliance and adherence, so maintaining motivation is thus central to long-term functional success of a therapy program. A promising methodology is to combine exercise with computer games, making training a more engaging and enjoyable experience (Barry et al., 2014). Digital media in the form of computer games can also challenge and improve many different aspects of executive cognitive function (Strenziok et al., 2014; Bonnechère et al., 2020). Many common and modern computer games are readily available in which processing speed, cognitive inhibition, task switching, working memory, and problem-solving are main components of interactive game play.

There is a need to develop and validate a low-cost platform that combines walking and executive cognitive activities. For this purpose, our research group has developed and validated an engaging cognitive game-based treadmill platform (GTP) for DT training, which includes an automated assessment subsystem (Nankar et al., 2017; Szturm et al., 2017; Ahmadi et al., 2019; Mahana et al., 2021). The GTP provides an integrated approach to address the decline in balance, gait, visuomotor, and executive cognitive functions. The GTP consists of: (a) a standard treadmill instrumented with a pressure mapping system to record center-of-foot pressure during walking, (b) an interactive computer game subsystem for DT; and (c) an automated monitoring application and analysis methods to quantify both gait and cognitive outcome measures (electronic records) while DT-walking.

At present, understanding of the neural underpinnings of DT-walking and training effects in PD is limited due to methodological limitations in neuroimaging (Monchi et al., 2004; Holtzer et al., 2014; Maidan et al., 2016). While diffusion tensor imaging (DTI) suggests that reduced white matter integrity—in pathways such as the forceps minor, corpus callosum, uncinate fasciculus, and cingulum—is associated with decreased gait stability and can indicate an increased risk of falling (Ghanavati et al., 2018; Snir et al., 2019), most neuroimaging data are limited to correlational analyses that take place in the absence of a walking task, or are limited in terms of spatial extent, such as functional near infrared spectroscopy (fNIRS). Some fNIRS investigations of walking have revealed that in healthy, able-bodied adults, prefrontal cortex (PFC) is bilaterally active and remains active during DT-walking as compared to single-task walking, whereas activation of the frontal lobe during DT-walking is impaired in persons with PD (Maidan et al., 2016). Recent functional magnetic resonance imaging (fMRI) studies have shown similar lack of PFC engagement during an executive function task (i.e., Wisconsin Card Sorting Task) in PD patients (Monchi et al., 2001; Nagano-Saito et al., 2014). It was suggested that basal ganglia degeneration affecting the striatum would result in less PFC activation during set-shifting in PD patients compared to the age-matched controls (Monchi et al., 2001).

Studies using resting fluorodeoxyglucose (FDG) positron emission tomography (PET) imaging have identified altered metabolic patterns in PFC and motor planning regions in PD that are associated with various gait abnormalities (and executive cognitive dysfunction (Fasano et al., 2015; Olchik et al., 2017). A few studies have examined FDG-PET in which the FDG uptake period involves either treadmill walking or overground walking (Shimada et al., 2013; Hinton et al., 2019; Mitchell et al., 2019a,b). FDG-PET imaging provides the unique opportunity to study functional imaging during interactions with different environments, in particular, during walking, because participants do not need to be constrained during the FDG uptake period. For example, PET imaging studies have been able to demonstrate a decline in sensorimotor cortical processing in middle-age during walking and obstacle negotiation (Mitchell et al., 2019b), and in PD patients with freezing of gait (Mitchell et al., 2019a). However, how DT-walking changes brain metabolism in PD has not been investigated. In this study, we will investigate behavioral analyses of gait and cognitive function, in addition to FDG-PET to assess a 10-week DT-walking training intervention, compared to treadmill walking only.

Although it is not possible to directly observe changes in brain function during a DT-walking task using MRI, this methodology can still provide important information regarding changes in brain structure and function at rest that can result following DT-walking training. Thus, in addition to the task-based PET imaging, pilot DTI and resting state data will be acquired—i.e., measuring brain function in the absence of an overt task—using both resting state fMRI (RS-fMRI) and pseudo continuous arterial spin labeling (pCASL). Although not much research has directly compared the relationship between gait impairment and functional connectivity—i.e., how different brain regions’ activity correlates over time—data suggest that PD patients with postural instability and gait difficulty have reduced functional connectivity in the cerebellum and putamen, compared to healthy controls (Chen et al., 2015; Ma et al., 2017; Tessitore et al., 2019). Furthermore, postural instability negatively correlates with functional connectivity in the putamen (Chen et al., 2015). Finally, using support vector machine-based [SVM, using an iterative single data algorithm (ISDA)] scores, our previous work shows that PD patients have similar metabolic and perfusion patterns (i.e., SVM-ISDA scores) as those with Alzheimer’s disease—importantly, these SVM-ISDA scores may be useful for monitoring disease progression and treatment response, and will be piloted in this study as a result (Katako et al., 2018).

## Material and Equipment

### DT Equipment

Both single-task (treadmill walking only) and DT conditions will use a standard treadmill instrumented with a pressure mapping system to measure center-of-foot pressure (Vista Medical Ltd., Winnipeg, MB, Canada). An interactive computer game system for DT will also be used, including a computer monitor for visual display (placed at the front of the treadmill), and a pool of 30 commercial games available from www.bigfishgames.com for the DT training program (see Supplementary Table 1 for a list and description of the games). Additionally, a miniature, wireless plug-n-play inertial-based computer mouse (IB-mouse; Therapy Mouse Mobility Research, AZ, United States) will be secured to a plastic headband and will allow interaction with the videogame system *via* head pointing movements (head rotation) to control the motion of any game sprite/paddle.

### Neuroimaging Equipment

Positron emission tomography images will be acquired using a Siemens Biograph mCT PET/CT scanner (Siemens Healthineers, Knoxville, TN, United States). Participants will be administered 185 MBq of [^18^F] FDG. For participants recruited in Winnipeg, MRI images will be acquired on a 3-Tesla Siemens/IMRIS MAGNETOM Verio MRI scanner (Erlangen, Germany), using a 12-channel head and neck coil. Participants recruited in Toronto will be scanned using a 3-Tesla, GE Discovery MR750 scanner.

## Methods

### Objectives

The aim of the proposed study is twofold. Behavioral analysis of gait and cognitive function together with PET and MRI brain imaging methods will be used to evaluate the molecular basis and neural underpinnings of (1) the decline of mobility function in PD, and (2) the effects of an engaging, cognitive game-based DT-walking program on mobility functions.

The first objective is to determine if the metabolic brain activity during single and DT treadmill walking is different in PD as compared to able-bodied age-matched controls. It is hypothesized that there will be significant changes in brain metabolic activity of several cortical and subcortical regions of the PD patients relative to able-bodied controls. This will be the case for both single and DT-walking conditions.

The second objective is to conduct a multi-centered, single-blind, randomized, two-arm, and parallel group-controlled trial and examine the effects of a 10-week DT treadmill training program: on (a) gate and cognitive function tested under single and DT conditions, (b) the pattern of metabolic brain activity quantified with single and DT-walking uptake periods, and (c) structural and functional changes (at rest) occurring prior to and after DT-walking training.

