### Participants

52 patients with PD [26 from Winnipeg, MB, Canada (site 1) and 26 from Toronto, ON, Canada (site 2)], and 15 age-matched healthy, able-bodied control subjects (site 1) will be recruited in a 2-year time period. The criteria used for recruitment of the patients will include; (a) diagnosis of PD according to United Kingdom brain bank criteria (Hughes et al., 1992), (b) stage II-III of PD according to the Hoehn and Yahr scale (Bhidayasiri and Tarsy, 2012), (c) age 50–75 years, (d) adequate vision to see required images on a standard computer monitor, (e) able to score 26 or greater on the Montréal cognitive assessment scale [MoCA (Marinus et al., 2011)], (f) on stable medications for the past 3 months, and (g) able to walk overground for 2 min without an aid or cane. The exclusion criteria for participation will include the following: (a) diagnosis of any psychiatric comorbidity or history of any other neurological disease other than PD, (b) any other medical condition limiting participant ability to walk on the treadmill, and (c) neuroimaging contraindications (i.e., claustrophobia, severe dyskinesia, diabetes, non-compatible metal implants, etc.). Healthy able-bodied adults with the same inclusion/exclusion criteria listed above except for diagnosis of PD will be recruited.

All responders to calls for participation will undergo a screening assessment. Ethics approval has been obtained from the institutional Human Research Ethics Boards. All volunteer participants will be asked to read and sign the informed consent form. The Clinical trial has been registered at ClinicalTrials.gov, identifier: NCT04415775.

Successfully screened PD participants will be randomized to the experimental intervention (XG) or an active control arm (CG). A computerized block randomization procedure will be implemented by an independent statistician. Randomization will be stratified by stage of the disease (Hoehn and Yahr stage II and III). To ensure similar representation of men and women, randomization will also be stratified by sex. Randomization will be achieved by having participants choose an opaque sealed envelope, each containing a group assignment.

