**FIGURE 1 F1:**
[figure not shown]
Experimental timeline. Assessment days (ADay) indicate order of assessments. PET scans on ADay_3_ and ADay_4_ will be counterbalanced between a single-task treadmill walking only task and a DT treadmill walking and cognitive game condition. A final DT PET scan will be acquired following intervention (ADay_7_). MRI scans will be collected pre- (ADay_2_) and post-intervention (ADay_6_). Behavioral testing (Behav; including motor measures and neuropsychological testing) will occur on three occasions: prior to intervention (ADay_1_), following intervention (ADay_5_), and again after a 6-month follow-up. Fall-history and physical activity tracking will be acquired throughout, until 12-months post-intervention. Measures of gait will be acquired throughout the program, including during behavioral assessment days, at each training session, and on PET assessment days. The experimental (XG) and control arm (CG) groups will complete the entire timeline, while healthy controls (HC) will complete up until ADay_4_.

Participants in the CG group will complete 10 weeks of a “single-task” exercise program including videogames only (i.e., for 10 min while sitting) and walking-only on the treadmill—these tasks are conducted independently, one at a time. Participants in the XG will perform various cognitive computer games during the warm up period on the compliant surface and during all treadmill walking intervals. The computer games will be played using the head mounted IB-mouse as described above. Many inexpensive and easily accessible common and modern games exist which are visually rich, fun, and engaging. They include a variety of tasks that require; (i) visual search and tracking of multiple targets, (ii) speed accuracy requirements, (iii) presence of distracters, (iv) matching tasks, and (v) working memory. Note that the games that will be used during behavioral and PET assessments and those used in the XG exercise program are different.

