A treadmill was chosen for the DT gait and cognitive functions for the following reasons. First, treadmill walking was chosen to overcome the confounding effect of gait speed. The treadmill allows the speed to be kept constant between walking conditions (single-task and DT), and over repeated measures (pre- and post-intervention time periods). This is of particular importance to standardize the uptake period of the PET imaging analysis at the three test periods. Most DT gait studies are performed overground, and all overground studies report a significant decrease in gait speed during the DT-walking condition, as compared to walk-only trials (Stegemöller et al., 2014; Raffegeau et al., 2019). Therefore, during overground DT-walking trials, there is a planned strategy to reduce the physical demands or threat to balance. Besides gait speed, many DT gait studies examine how cognitive demands affect gait rhythm and stability [i.e., recording spatiotemporal gait variables or analysis of trunk linear acceleration (Ijmker and Lamoth, 2012; Montero-Odasso et al., 2012; Asai et al., 2013; Martinez-Martin et al., 2013; Nankar et al., 2017; Ahmadi et al., 2019)]. However, gait speed is a confounding variable, as spatiotemporal gait variables and trunk acceleration are sensitive to changes in gait speed (Frenkel-Toledo et al., 2005; Jordan et al., 2007; Kang and Dingwell, 2008; Keene et al., 2016; Cole et al., 2017). Most overground DT-walking studies use an instrumented walkway, which records only 4–6 consecutive steps. It has been shown that using a continuous walking protocol, instead of short intermittent walks, and collecting more than 30 consecutive steps improved reliability, in particular for measures of gait variability and during DT-walking trials (Bruijn et al., 2009; Hollman et al., 2010; Galna et al., 2013). In addition, there is a limited choice of executive cognitive tasks that can be assessed during the short time period to walk a few meters. For example, cognitive tasks used during overground walking include walking while talking, recall of names/words, serial subtraction, or auditory Stroop (Stegemöller et al., 2014; Gregory et al., 2017; Ghanavati et al., 2018; Raffegeau et al., 2019; Snir et al., 2019). The present study extends these assessments to include visuomotor and visuospatial cognitive tasks assessed over a 1-min time period. Tracking visual objects and processing of what is being seen are important cognitive functions to consider in the analysis of DT interference on mobility (Nagamatsu et al., 2009; Logan et al., 2010). Cortical areas devoted to visual spatial ability such as the frontal and parietal lobes may be particularly susceptible to the neurodegenerative process of PD (Battisto et al., 2018; Lally et al., 2020). Following the principle of neural overlap (Crockett et al., 2017), DT interference should be greatest when the cognitive and motor tasks engage the same neural circuits and processing resources, e.g., visual-spatial processing. Walking endurance will be evaluated with a 6-min walk test [6MWT (Combs et al., 2014)]. Overground walking speed will also be evaluated over 25 m in a straight corridor.

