#### Image Acquisition

##### PET Data

All subjects will undergo two pre-intervention [^18^F] FDG-PET scans after fasting for at least 6 h before scanning. A head CT scan will be acquired for attenuation correction purposes. Static images (10 min) will be acquired starting 40 min after injection. During the FDG uptake period, participants will perform in different sessions, on different assessment days; (a) treadmill walking only (test session 1) and (b) DT treadmill walking (test session 2; see Figure 1). The order of the walk-only and DT-walking sessions will be counterbalanced. The single and DT treadmill walking will be done for 28 min each. This will involve seven 3-min walk intervals with 1-min rest periods (standing). Walking speed and duration will be carefully controlled, and repeated for each test session (i.e., single and DT conditions, pre- and post- intervention). Seven different standardized cognitive games will be selected for the seven DT-walking intervals. These will include; (a) five 3-min VC games with different difficulty levels (i.e., increasing game speed, adding distractors, and changing path of target motions), and (b) two 3-min VMT games, one played using horizontal head rotations and one with vertical head rotations. The PD patients will repeat the DT-walking PET imaging protocol after completion of the 10-week exercise program.

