##### pCASL Analysis

For the pCASL images, the preprocessed cerebral blood flow (CBF) images will be assessed using SVM-ISDA, which will be used to train a classifier that separates patients into PD patients with normal cognition, and those with mild cognitive impairment. The pCASL data will be analyzed by Machine-based Alzheimer’s disease Designation (MAD) to compute Alzheimer’s-like pattern expression scores (Katako et al., 2018). High scores in metabolic/perfusion patterns indicate similarity with Alzheimer’s patients—we have previously shown that PD dementia patients show similar brain metabolic patterns and that perfusion imaging may replace FDG-PET imaging when MAD is applied (Katako et al., 2018). Our recent work suggests the utility of using SVM-ISDA-based scores for monitoring disease progression in repeated measures designs. Changes in these scores will be used to assess the neural correlates of the treatment response.

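### Objective 2(b) claims training effects on PET under single and dual-task walking, but only a dual-task scan follows training; a minor second point is a pCASL classifier whose impaired class is undefined and probably small

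*Protocol article*

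**What the plan says.** **PET.** Under Objectives, the second objective lists, as item (b), the effect of the 10-week programme on "the pattern of metabolic brain activity quantified with single and DT-walking uptake periods". The schedule is given in several places:
- PET Data, before training: "All subjects will undergo two pre-intervention [^18^F] FDG-PET scans after fasting for at least 6 h before scanning", one with walking only and one with DT walking during uptake.
- PET Data, after training: "The PD patients will repeat the DT-walking PET imaging protocol after completion of the 10-week exercise program".
- Figure 1 legend: "A final DT PET scan will be acquired following intervention".
- Motor and Gait Assessment, in the reasons for using a treadmill: the aim is to "standardize the uptake period of the PET imaging analysis at the three test periods".
- FDG-PET Analysis: the longitudinal pattern compares the post-training with the pre-training DT scan only.

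One phrase in PET Data points the other way. Walking speed and duration are to be held fixed and "repeated for each test session (i.e., single and DT conditions, pre- and post- intervention".

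For the tests, Statistical Analyses gives paired-sample t-tests, with age and gender as regressors of no interest, for the imaging modalities. FDG-PET Analysis gives a post-versus-pre pattern. Neither names a comparison of PET change between XG and CG.

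**pCASL.** The pCASL Analysis section will use the blood-flow images to "train a classifier that separates patients into PD patients with normal cognition, and those with mild cognitive impairment". Under Participants, patients must be "able to score 26 or greater on the" MoCA scale. The same pCASL section also plans an Alzheimer's-like (MAD) pattern score.

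**The concern.** Anticipated and Preliminary Results predicts that DT training will specifically change the abnormal DT-related metabolic pattern. FDG-PET Analysis defines that pattern in patients as DT versus single walking before training. Without a single-task scan after training, that contrast cannot be formed again. A change seen on the DT scan may reflect altered metabolism in walking generally, an altered cost of the second task, or both. A purely pre-post test adds to the difficulty, because both arms walk on a treadmill for 10 weeks and any effect common to them stays in the estimate. A report written to Objective 2(b) as worded could claim more than the data hold.

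For pCASL, training a classifier needs enough labelled members of each class. The sample is selected on a cognitive score and is then expected to supply a cognitively impaired class, so one class may be too thin to train on.

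**Working it through.** **1. Scan count per patient** (PET Data; Figure 1 legend)

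| Uptake condition | Before | After |
|---|---|---|
| Single-task walking | 1 | 0 |
| DT walking | 1 | 1 |

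Total: 1 + 1 + 0 + 1 = 3, which reproduces the three PET test periods stated under Motor and Gait Assessment. With 52 patients:
- pre/post DT pairs: up to 52 × 1 = 52;
- pre/post single-task pairs: 52 × 0 = 0.

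**2. What the scans identify.** For a region or pattern score, let S be the single-task value, D the DT value and C = D − S the DT cost. Write Δ for change from before to after training. Then

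ΔD = ΔS + ΔC.

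Only ΔD is observed. S after training is missing for every patient, so ΔS and ΔC cannot be separated.

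**3. What a between-arm comparison adds.**

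ΔD(XG) − ΔD(CG) = [ΔS(XG) − ΔS(CG)] + [ΔC(XG) − ΔC(CG)].

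A walking or fitness effect of equal size in both arms cancels from the first bracket. It does not cancel from ΔD in a paired test within an arm or in the arms pooled. If the arms differ in ΔS as well as ΔC, even this contrast does not split the two. It remains a valid randomised estimate of the effect on metabolism during DT walking.

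**4. Expected size of the MCI class.** The article gives no MCI rate for patients with a MoCA of 26 or more, so the rate p is an assumption. Expected cases are 52 × p, and the last column is the exact binomial probability of at least 10 cases.

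| Assumed p | Expected MCI cases of 52 | P(at least 10) |
|---|---|---|
| 0% | 0 | 0 |
| 5% | 2.6 | <0.001 |
| 10% | 5.2 | 0.03 |
| 20% | 10.4 | 0.61 |

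Ten is only a marker for comparison, not a requirement taken from the article.

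**The case against.** **PET.** The schedule itself is coherent: the legend, the acquisition text, the count of three periods and the longitudinal analysis all agree on a DT-only scan after training. The conflict lies in the wording of one objective. That wording can also be read more gently: a pattern derived from the baseline single-versus-DT contrast is scored on every image, including the post-training DT scan. This is deliverable, so a reader who infers that the whole PET objective fails goes too far. It is not the plain sense of 2(b), though, and it yields no single-task or DT-cost change.

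A reader might also take the phrase "repeated for each test session (i.e., single and DT conditions, pre- and post- intervention" as promising a training effect under both conditions. It does not. The sentence is about keeping speed and duration constant, and it schedules no fourth scan.

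The control arm is the strongest reply. CG also completes 10 weeks of treadmill walking, and speed is fixed across sessions, so comparing arms would deal with general walking effects. That stands only if the arms are compared, and the PET tests as written do not do so.

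**pCASL.** One might infer that patients with MCI are excluded at entry and the classifier is impossible. The article never equates a MoCA below 26 with MCI and does not list MCI as an exclusion. CANTAB is collected, and a full protocol could attach an MCI definition to it. Nor is it clear that the treatment-response analysis relies on the MCI classifier: the sentence about changes in scores follows the MAD and SVM-ISDA text and may refer to those scores. The MAD analysis is unaffected. What remains is that the article selects on cognition, plans to train on cognitive impairment, and names no external training cohort.

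**Conclusion.** The PET point holds. Objective 2(b) is wider than the scans: 0 of 52 patients can contribute a change in single-task metabolism or in the DT-minus-single contrast. This rests on the article's own schedule and needs no outside assumption. The longitudinal DT analysis can be carried out, but as written it is a pre-post test from which a general walking effect has not been removed. The text should be corrected before analysis because the correction changes what the trial can conclude.

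The pCASL point holds in a limited sense and is minor. The MCI class is undefined in the article and probably empty or small: about 0 to 5 of 52 if 0 to 10% have MCI, about 10 if 20% do. That range is assumed, and the article calls its MRI data pilot data. Neither point touches the randomisation or the behavioural outcomes.

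**What to change.** 1. Restate Objective 2(b) as the XG-versus-CG difference in pre-post change in metabolism during DT walking, including change in the baseline-derived pattern scores.
2. Write the matching PET analysis as a comparison of change between arms, beside or in place of the paired tests.
3. Make no claim about post-training change in single-task metabolism or in DT cost.
4. Align the speed-and-duration phrase in PET Data with the DT-only post-training scan.
5. In pCASL Analysis, drop the training of a normal-versus-MCI classifier in this sample, or train it on a named external cohort. Rely on the planned Alzheimer's-like MAD/SVM-ISDA score and compare its change between XG and CG, which matches the larger XG effect already hypothesised.

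The cost is rewording an objective and a few analysis sentences. No new scans are needed. Keeping 2(b) as worded would instead require a fourth PET session per patient, up to 52 more scans.
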